### Data Management

All data are managed on secure servers through the data coordinating site via a central database or through site-based collection measures. All participants are registered with an identification code. Source data includes any original documentation to the study. The database is monitored by the data coordinating site and kept current to ensure monitoring of data and appropriate follow-up of participants throughout the study protocol. Monthly, quarterly, and individual injury monitoring occurs across the entire study period by the data coordinating site to ensure data quality and timely entry.

### Study Outcomes and Assessments

The primary trial endpoints include time to asymptomatic/symptom free and time to full clearance for return to sport, in days. The secondary endpoints include clinical and quality of life outcomes assessed from baseline through 1-month post return to play, as well as safety and feasibility outcomes. An assessment protocol similar to the NCAA-DOD Grand Alliance Concussion Assessment, Research, and Education (CARE) Consortium's is utilized for both baseline measurements and post-injury assessments and to achieve the primary and secondary endpoints (15). The assessment time-points for the study (Table 3) include: pre-season baseline, time of injury (optional, 24–48 h following injury, daily symptom and activity tracking through 7 days post-return to play, athlete satisfaction at 7 days post-return to play, and 1-month following full return to play. Each of the assessment timepoints are collected at the approximate windows, i.e., within 5 days, due to the nature of athletic schedules. Study measures are administered by trained site personnel and clinicians. Assessments take place at site medical and training facilities. Below are brief descriptions of all study measures.

**Table 3 T3:** Assessment schedule.

	**Demographics**	**Personal and family history**	**SCAT symptom checklist**	**QOL**	**BSI-18**	**Neurocognitive assessment**	**SAC**	**BESS**	**NPC**	**Dual-task**	**Start and end fatigue rating**
**Pre-season baseline**	✓	✓	✓	✓	✓	✓	✓	✓	✓	✓	✓
**Time of injury (within 6 h—if possible)**			✓				✓	✓			
**24–48 h post-injury**			✓		✓	✓	✓	✓	✓	✓	✓
**Asymptomatic post-injury**			✓	✓	✓	✓	✓	✓	✓	✓	✓
**1-month post return to play post-injury**			✓	✓	✓	✓	✓	✓	✓	✓	✓
- Symptoms and activity assessed daily from the first assessment point until 7 days post return to play - Concussion Index completed following injury - Recovery Form completed following return to play - *Participant Satisfaction completed at 7-days post return to play*											

*QOL, Quality of Life; BSI-18, Brief Symptom Inventory 18 item; SAC, Standardized Assessment of Concussion; NPC, Near Point of Convergence; SCAT, Sport Concussion Assessment Tool*.

**Demographics**: Demographic information is collected on a separate form depending on the study cohort (i.e., High School, College/University, and Professional Setting). This assessment includes standard demographic information such as date of birth, sex at birth, place of birth, and race. In addition, information regarding sports history and academic level/achievement will be collected. *Time point collected: Baseline*.

**Concussion History**: The concussion history form provides the participant with a definition of concussion prior to asking the participant to provide a self-report of concussion history. Participants are directed to a concussion summary report for each concussion they report to have experienced. In the summary report the participant is asked to identify whether the concussion was sport-related or not, if the concussion was diagnosed, the approximate date of injury, their age at the time of injury, whether or not they lost consciousness (for how long), if they experienced any form of amnesia, and the number of days they experienced symptoms related to this particular concussive injury. *Time point collected: Baseline*.

**Medication History**: The medication history form requires the participant to identify any prescription medications she/he is currently taking as well as any over the counter medications. Prescription medications are broken up into categories (antidepressants, anti-psychotics, narcotics, non-narcotic pain medication, sleep aids, psychostimulants, birth control, allergy medication, asthma medication, and medication for acid reflux). The participant is asked to identify the exact name of any type of medication they are currently using. Three over the counter medications are listed for the participant to identify using including ibuprofen, acetaminophen, and loratadine. The participant is given space to identify any other over the counter medications they are currently using that are not listed. Lastly, the participant is asked to identify any supplements they may be using, and to report their tobacco, marijuana, and alcohol use. *Time point collected: Baseline*.

**Medical History**: The medical history form contains questions regarding the following self-reported information: height, weight, handedness and headache history. Participants are also asked about diagnosis of the following: meningitis, seizures, diabetes, sleep disorders, balance disorders, vestibular disorders, vertigo, motion sickness, Meniere's disease, psychiatric disorders, and other conditions. Participants are asked to provide information regarding previous diagnosis of conditions such as: learning disorders, attention deficits, hyperactivity disorder, vision and hearing issues, stroke, Parkinson's, and memory disorders. Participants also report any family history of headaches, migraines, Parkinson's, and memory disorders. Lastly, participants are asked to report their sleep patterns. *Time point collected: Baseline*.

**Symptomology**: The Standardized Concussion Assessment Tool symptom checklist (3, 16) includes a 22-item symptom inventory, self-reported hours of sleep inquiry, and questions regarding factors that may influence the severity of a participant's symptoms (i.e., mental/physical activity). Each participant is asked to rate how they feel “on a normal day” at baseline and “now” post-injury, with respect to each particular symptom, on a 6-point scale ranging from “none to severe” (0–6, respectively). Reliability and validity of the symptom checklist is well-established (20). Each symptom item score is added together to determine overall symptom burden (symptom severity score); higher scores indicate greater symptom burden (severity). For this study, a reliable change is considered as a change of 10 points or more (18, 19). The possible score range for burden is 0–132. (*Time points collected: Baseline, Time of Injury, 24–48 h post injury, Asymptomatic, and 1-month post return to play. Note that participants who are injured and enter into the post-injury protocol are also asked to complete symptom checklists at the beginning and end of each intervention session*.

**Brief Symptom Inventory-18 (BSI-18):** Psychological distress is measured utilizing the BSI-18. The BSI-18 is a brief symptom inventory with high reliability (21). The assessment gathers athlete-reported data to help measure psychological distress in primary care settings (21). Participants rate their level of distress associated with 18 symptom items on a scale from 0 (not at all) to 4 (extreme). Ratings are then added together to compute an overall symptom distress score. *Time points collected: Baseline, 24–48 h Post-Injury, Asymptomatic Post-Injury, and 1-month post return to play*.

**Health-Related Quality of Life (HRQL**): Participants' HRQL is assessed using the Athlete-Reported Outcomes Measurement Information System (PROMIS-29), and the Quality of Life in Neurological Disorders (Neuro-QOL) Cognition and Fatigue Scales. These scales have high reliability and validity concerning overall quality of life (22–24). Outcomes will include the PROMIS-29 and Neuro-QOL summary scores (anxiety, physical function, depression, sleep disturbance, social role/activities, pain interference, pain intensity, Neuro-QOL cognition, and Neuro-QOL fatigue). These scales ask the participant to rate items on a Likert type scale ranging from 1 to 5 (higher or lower score indicating “worse” is dependent upon the item). *Time points collected: Baseline, Asymptomatic, 1-month post return to play*.

**Computerized Neurocognitive Testing**: Participant neurocognitive performance at baseline and post-injury will be assessed utilizing the computerized neurocognitive testing platform currently used clinically at each site. The platforms to be included by study sites include Immediate Postconcussion Assessment and Cognitive Test (ImPACT), CogSport, and Concussion Vital Signs. Reliability and validity of computerized tests varies and has been established in previous literature (25, 26). Each platform includes alternating forms and presentation variation. *Time points collected*: *Baseline, 24–48 h post injury, Asymptomatic, and 1-month post return to play*.

**Mental Status**: The Standardized Assessment of Concussion (SAC) (varied forms) (27, 28) will be used to assess mental status. The SAC is a clinical measurement to determine an individual's cognitive orientation, concentration ability, and immediate/delayed memory recall. The SAC has been shown to be a reliable and sensitive measure of concussion (27, 28). Alternate forms are used at each time point. *Time points collected: Baseline, Time of Injury, 24–48 h post injury, Asymptomatic, and 1-month post return to play*.

**Balance**: Balance is assessed utilizing the Balance Error Scoring System (BESS), as it is an objective postural stability measure that can be implemented in an office, field, or clinic setting. The test is administered as the participant completes three 20 s stance trials (i.e., double leg, single leg, tandem stance) on firm and foam surfaces (Figure 6). The administrator tracks errors during the trials. The BESS has been shown to have high reliability and sensitivity and specificity (30). The outcome from the BESS will be the total error score. *Time points collected: Baseline, Time of Injury, 24–48 h post injury, Asymptomatic, and 1-month post return to play*.

**Figure 6 F6:**
[figure not shown]
Balance Error Scoring System (BESS) stances. Written informed consent was provided by the individual in the image for publication. **(A)** Double leg firm, **(B)** single leg firm, **(C)** tandem stance firm, **(C)** double leg foam, **(E)** single leg foam, and **(F)** tandem stance foam (29).

**Near Point Convergence**: The Near Point of Convergence (NPC) test will function as the visual/oculomotor exam for this study (31). NPC is measured by drawing a tongue depressor with a dot in 14-point font from arm's length toward the participant's nose. The participant is instructed to stop the approximation at the point the visual target is seen in double (diplopia). The clinician then measures the distance between the tip of the nose and the tongue depressor in centimeters. Three trials are collected and averaged. NPC has been shown to be a reliable measure (32). *Time points collected: Baseline, 24–48 h post injury, Asymptomatic, and 1-month post return to play*.

**Dual-task**: Dual-task performance will be assessed via the Walking and Remembering Dual-Task Assessment (ISAW-Grid Task) (33) which has been previously reported as potentially useful for physically active individuals (34) and evaluates divided attention cost across a gait and cognitive task. Participants walk 3.5 m toward a target and then turn and walk back to the start line and the walk time is recorded. Participants are then given 2 numbers and 6 letters from the military phonetic alphabet and asked to recall the information accurately and in order. Alternate word list are given at each time point. Following these single tasks, the individual is then asked to combine the task. The examiner gives the individuals 2 numbers and 6 letters to remember, the participant completes the gait task, and upon return to the start line, the participant is asked to recall the numbers and letters (Figure 7). Gait time and accuracy are scored and coded as the initial outcomes. Performance in the dual-task is then compared for each of these outcomes to the single task, yielding the primary outcome of dual-task cost. Participants will be asked to complete a cognitive (immediate recall) task while also completing a walking task of 7 m. *Time points collected: 24–48 h post injury, Asymptomatic, and 1-month post return to play*.

**Figure 7 F7:**
[figure not shown]
Dual-task schematic. **(A)** Memory task begins, **(B)** walking task, and **(C)** memory recall.

**Daily Activity and Symptom Tracking**: All concussed participants complete a daily activity and symptom tracking survey (cognitive and physical) from time of injury through 7 days post return to play. The survey can be completed on paper or via Qualtrics and includes questions about mental and physical activity as well as symptoms. *Time point collected: Daily through 7-days post return to play*.

**Participant Satisfaction**: The participant will be asked to complete a questionnaire regarding his/her satisfaction with the rehabilitation sessions and the intervention. This measure is adapted from the PSQ-18 which is a publicly available scale that measures general athlete satisfaction with care. The PSQ-18 was designed based on feedback from athletes using input from providers about the care they receive and has been used in various settings. *Time point collected: 7 days post return to play*.

**Concussion Injury Index**: This form documents all aspects of a participant's concussion. It is completed by the clinical research staff at the study site. Information gathered on this form includes: sport at time of injury, number of years playing sport, date and time of injury, date reported injury, loss of consciousness, etc. *Time point collected: This form is to be completed over the course of the injury and should be finalized by the 1-month post-return to play time point*.

**Recovery Tracking**: A recovery tracking form documents all aspects of a participant's recovery from a concussion. It is completed by the clinical research staff at the site throughout the time it takes the participant to recover. Length of symptoms, medication usage, therapies/treatments, psychiatric issues, and return to play information will be reported. It also includes information on completion or discontinuation of the study treatment activities (e.g., discontinuation of the intervention for medical reasons). *Time point collected*: *This form should be completed over the course of the injury and should be finalized by the time entry is completed for the 1-month post-injury assessment*.

### Planned Data Analysis

We conduct quarterly, interim analysis for descriptive outcomes to determine continued safety and feasibility of the study and to prepare safety reports.

***Specific Aim 1***
*(evaluation of effectiveness):* For analyses of our primary endpoints, Cox proportional hazards regression models (35) will be used to compare time to return to play and time to asymptomatic between the EGE and MDR groups. The specific outcomes for the Cox models will be time from date of injury to: (1) date of medical clearance for full return to participation and (2) asymptomatic date. The Wei-Lin robust variance estimator will be used to account for the effect of cluster-randomization by site (36).

For our secondary endpoints (clinical and quality of life measures), recovery trajectories will be examined by use of General Linear Mixed regression models and non-parametric smoothers. Random effects will be utilized to account for the effect of clustering by site and the effect of repeated observations over time within an individual participant. The time axis to be modeled in both sets of analyses is time from initiation of the treatment (defined as stable symptoms for 24 h), and time will be treated as a continuous variable in all analyses.

We will also assess potential predictors of attrition (e.g., gender, race, socioeconomic status). If no predictable patterns are observed for missing data (i.e., missingness occurs at random), no imputations will be conducted. Inverse probability of attrition weights based on the factors influencing attrition will be used to account for potential selection bias due to attrition. We will assess the differences between the EGE and MDR group participants (those with SCR) at baseline and before starting the treatment protocol.

For sensitivity analyses of primary and secondary, we will conduct intent-to-treat analysis (prescribed treatment), per-protocol analysis (adhered treatment) and use inverse probability weighting to determine potential outcomes had everyone adhered to their prescribed treatments.

To test the effectiveness of randomization, we will compare key variables at baseline and immediately post-injury (24-48 h timepoint) to determine differences between arms. These variables at a minimum will include: age, gender, previous history of concussion, contact/collision sport, baseline symptom severity score, 24–48 h symptom severity score. Should any differences be observed these factors will be controlled for in the models. Additionally, 24–48 h symptom severity will be considered in all analyses.

***Specific Aim 2*** (safety and feasibility): We will utilize descriptive statistics, qualitative analyses for open ended text of perceptions (exploratory based; triangulation) to understand overall safety, adverse event prevalence, and protocol perceptions.

***Sample size*** (determined based on primary outcomes): Given that each participant will be recruited between 6 and 48 h post-concussion and will be followed for a month after their return to play (average total time of ~37 days), if we estimate that each arm will have at least 100 participants, we will have 83% power to estimate an effect size of 0.64 in the MDR group as compared to the EGE group concerning days to asymptomatic. Table 4 shows the available power for varying sample and effect sizes.

**Table 4 T4:** Power and effect size based on number of participants in each arm.

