### Allocation to Study Arm

The two treatment arms (multidimensional active rehab and EGE progression) are assigned at random to the 28 sites in the study. Site level (cluster) randomization is utilized because the study team considered that patient-level randomization at a site would be prone to contamination between arms. Thus, all athletes at a given site receive the same protocol. All study sites are randomized to either the MDR (early rehabilitation) or the EGE [current return to sport strategy (16)]. To ensure a balanced of treatment arms across cohort, site randomization is stratified by (i.e., conducted within) cohort (NZR, CFL, College, HS). Colleges/universities and high school sites are stratified by size of school prior to randomization; CFL and NZR sites are not stratified. Due to the nature of the early and active treatment delineation, no allocation concealment such as masking or blinding is possible. The clinicians (site personnel) at the sites know their allocated arm. However, participants are not explicitly told about the role of their respective study arm. Site personnel at the MDR sites are trained to deliver the treatment separately from the site personnel at the EGE sites.

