**Return to full participation**		
Return to full participation will occur at the physician/site medical professional's discretion of patient full recovery and will be documented. The intervention progression will stop.		

Specifically, progression from one phase to the next in Phases II through V requires that the participant does not experience any significant increase in symptoms from the beginning of one intervention session to the beginning of the subsequent session (as measured by a RCI of 10 of more total severity point increase), and no symptom score at the beginning of an intervention session is a 5 or 6 on the self-reported symptom severity scale. Once determined to be clinically recovered (“asymptomatic” by study definition or at clinician discretion), they begin the EGE progression (16) (Table 1) with sport and skill specific enhancements at each phase. This MDR protocol should not delay the return to play process as when the participant becomes “asymptomatic” (by the study definition) they begin the enhanced graded return protocol (as the standard of care states) and will continue MDR exercises throughout this process. MDR activities are integrated with the return to sport progression at each Stage once the return to sport progression begins (Figure 4). Participants continue the rehabilitation progression during the EGE protocol and may continue the MDR exercises after full return for maintenance and/or to complete the last phases of the MDR progression at their clinician's discretion. Figure 5 provides an example of cognitive activity progressions through each Phase. The Supplemental Table 1 outline activity “bucket” progressions by MDR phase.

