### Safety Procedures

As with any trial, safety-related procedures were decided *a priori* by the study team in concordance with current literature. Potential risk of the study assessments and interventions were evaluated. Based on previous studies and clinical fortitude, it was determined *a priori* that discomfort is likely (10–25%) to occur as the participants are progressed in the interventions. We specifically anticipated more discomfort among those in the multidimensional activity group, as discomfort may increase slightly during rehabilitation sessions, as often occurs within any type of rehabilitation session. All rehabilitation is monitored and progressed by medical professionals and individuals are referred to their team physician as deemed medically appropriate. If at any point the participant or clinician feels the intervention should be discontinued, this is done and documented. Injury risk is rare, however, there is the small possibility that symptom exacerbation or injury may occur during the interventions or testing. As all participants will be studied and progressed in environments with medical professionals, any potential significant symptom exacerbation or injury is documented, and participants are referred to the physician at the institution as deemed appropriate. The physician and medical team at each site will determine status and ability to continue the study activities. All events of this nature are documented appropriately via study administrative forms. A symptom-based adverse event was determined to be, as outlined in the progression, if an individual's symptoms increased by a reliable change of 10 or more points and remained elevated at that change in the subsequent session. An independent safety officer reviews quarterly study safety reports provided by the study team study and provides feedback on any overall concerns or safety issues. If the safety officer deems the study unsafe after corrective actions have been put into place, the study will be halted, or significant changes may be made to the study methods.

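### Clearance counts as success from its date, but the defined symptom adverse event normally stops at clearance, so symptom harm after return is captured only indirectly and not equally in the two arms

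*Protocol article*

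**What the plan says.** Under Specific Aim 1, one of the two primary Cox outcomes is time from injury to the "date of medical clearance for full return to participation". The other is time to the asymptomatic date. Neither carries a condition that the state must last.

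Table 2 says who decides: "Return to full participation will occur at the physician/site medical professional's discretion of patient full recovery and will be documented". The next sentence there reads "The intervention progression will stop". The text below the table lets MDR athletes carry on with their exercises after full return if the clinician wishes. Allocation to Study Arm states: "The clinicians (site personnel) at the sites know their allocated arm".

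Safety Procedures defines a symptom-based adverse event as occurring "if an individual's symptoms increased by a reliable change of 10 or more points and remained elevated at that change in the subsequent session". It also says "there is the small possibility that symptom exacerbation or injury may occur during the interventions or testing", and that such events are documented. Specific Aim 2 plans descriptive and qualitative analyses "to understand overall safety, adverse event prevalence, and protocol perceptions".

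Data after clearance do exist. The daily activity and symptom survey runs "from time of injury through 7 days post return to play", and Table 3 schedules a full battery 1 month after return to play.

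**The concern.** Earlier clearance is a benefit only if the athlete stays well after it. Here an unblinded clinician judges the event, and the event is credited on its date whatever follows. The natural safeguard is a count, by arm, of athletes whose symptoms came back after return. The article defines a symptom event, but in terms of consecutive sessions, and sessions usually finish when the clearance endpoint is reached. An athlete who worsens on day 3 after return would normally not meet the definition.

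There is also an asymmetry. MDR athletes who continue their exercises still have sessions and can still meet the definition. EGE athletes have no corresponding option. A comparison of event counts would then mix true differences with differences in the opportunity to be counted.

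At stake is the reading of a positive clearance result. If MDR athletes are cleared sooner, the planned outputs give little direct evidence on whether those clearances held.

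**Working it through.** **Step 1. The plan's own figure.** Sample size quotes 83% power at 100 per arm for a ratio of 4.5/7 = 0.64. Alpha is not stated, so two-sided 0.05 is assumed. By Schoenfeld's formula, power = Φ(√(D/4) × |ln HR| − 1.96), with |ln(4.5/7)| = 0.442.
- D = 200 events: √50 × 0.442 − 1.96 = 1.16, power 87.8%.
- D = 180 (10% attrition): √45 × 0.442 − 1.96 = 1.00, power 84.2%.
- D = 170 (15% attrition): √42.5 × 0.442 − 1.96 = 0.92, power 82.1%.

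The 83% is reproduced with the article's own 10–15% attrition. It concerns time to asymptomatic. The article gives no effect size for clearance, and the present point does not depend on this figure.

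**Step 2. What can be counted, before and after clearance.**

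| | EGE | MDR |
|---|---|---|
| Sessions before clearance | graded exertion sessions, symptom checklist at start and end | MDR sessions, then MDR integrated with graded exertion |
| Sessions after full return | none provided for | optional |
| Defined symptom event possible after full return | normally no | yes, if exercises continue |
| Daily symptom survey to day 7 | yes | yes |
| 1-month battery | yes | yes |

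The last two rows apply equally to both arms, but no section turns them into an athlete-level event. Study Arms and Treatment Protocols uses the activity log for compliance and as a source of covariates. The 1-month measures enter the mixed models as trajectories.

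**Step 3. Can the 1-month mean stand in for the missing count?** Inputs: 100 per arm less the article's 20–30% attrition at 1 month gives 80 to 70 per arm. Assumed: SD of 8 to 12 points on the symptom score, and no clustering. If a proportion x of extra athletes in one arm are each k points worse at the visit, the mean shifts by Δ = x × k, and power ≈ Φ(Δ / (SD × √(2/n)) − 1.96).

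| Excess x | Points k | Shift Δ | Power (n 70–80, SD 12 to 8) |
|---|---|---|---|
| 10% | 10 | 1 | 7–12% |
| 20% | 10 | 2 | 17–35% |
| 20% | 20 | 4 | 51–89% |

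Example: n = 70, SD = 12, Δ = 1 gives 1/(12 × 0.169) − 1.96 = −1.47, power 7%. A modest excess would probably be missed. A large one that lasts to the visit could show. Worsening that resolves before the visit leaves little trace in it.

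**Step 4. Illustration of how far early clearance could move the primary result.** All distributions are assumed: no recovery difference, 88 observed per arm (100 less 12%), exponential time to asymptomatic with median 7 days, then 4 days plus a gamma time of mean 2 days, rounded up to whole days. Athletes are independent, and the log-rank test is judged at one-sided 2.5% in favour of MDR.

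| MDR clearance earlier by | Shift applied to everyone | Same shift, 4-day minimum kept in both arms |
|---|---|---|
| 1 day | about 10% | about 8–10% |
| 2 days | about 24% | about 12–20% |
| 3 days | about 44–47% | about 15–25% |

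The ranges reflect simulation error and gamma shapes 1 to 4. The right-hand column respects the model's own minimum for graded exertion and is the more coherent one. The simulation contains no relapses. It shows only that a shift in clearance dates of this size, without better recovery, can be declared a benefit more often than the nominal 2.5%. The planned site-robust variance is not modelled.

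**The case against.** The strongest reply is that the plan already has several protections. Time to asymptomatic is also primary, rests on a symptom score, and would not move if only clearance were early. A gain in one without the other would be a warning. Serious adverse events are reported, an independent safety officer reviews quarterly reports, a separate safety paper is planned, and secondary measures run to 1 month after return. The sentence about injury during interventions or testing describes a risk. It does not limit what counts as safety. The full protocol is not shown and may define relapse or re-injury. Table 1 also places a medical clearance before full contact practice, so if that is the clearance used, some graded sessions might follow it.

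Most of this stands, and it limits the point. A reader might infer that a premature-return arm would be reported as effective with clean safety. The documents do not support that: serious or lasting harm has routes to be seen. A reader might also infer that premature clearance is happening, or that Table 4 sets the expected gain in clearance days. Nothing shows the former, and Table 4 is headed time to asymptomatic.

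The session-based definition is not answered. The article itself fixes that definition, so this is more than detail left to another document. The asymptomatic endpoint also ends at a single date and counts no return of symptoms.

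**Conclusion.** The point holds in limited form. Clearance is discretionary and unblinded, and it is credited from its date. The only defined symptom event depends on sessions that normally end at full return, with an optional continuation in MDR alone. Symptom harm after clearance is therefore measured indirectly, and the chance of being counted differs by arm.

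On an assumed SD of 8 to 12 points and no clustering, the 1-month mean has about 7–12% power against a 10% excess at 10 points, and 51–89% against a 20% excess at 20 points. Clustering would probably lower both. The illustrative false-benefit rates (about 8–10%, 12–20% and 15–25% for clearances 1, 2 and 3 days early with the 4-day minimum kept) depend wholly on assumed distributions and do not estimate what will happen in this trial.

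This is a gap in outcome definition. It is worth closing before the clearance result is interpreted, and it does not invalidate the design.

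**What to change.** 1. Extend the analysis definition of the symptom adverse event past clearance, identically in both arms. Count each athlete with a rise of 10 or more points (the trial's own reliable change) on the daily symptom record through 7 days after return, relative to the last rating at or before clearance. First confirm that the daily record uses the 22-item scale on which the 10 points are defined, since its description mentions symptoms without naming the scale.
2. Report that count by arm, with a site-clustered 95% CI for the difference, beside the clearance result.
3. List new sport-related concussions before the 1-month post-return visit separately. They depend on exposure and are not necessarily failed clearances. State that this visit is timed from return to play, because the Abstract and Recovery Tracking label it as post-injury.
4. Optionally, add a sensitivity Cox analysis that does not count clearances that fail, but only if dates of withdrawal and re-clearance are recorded. No section says they are.

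Items 1 and 2 need analysis wording only, if the scale is confirmed. Item 3 may need one item on the 1-month form. No treatment or clearance rule changes. The drawback is few events and a wide interval, so the result should be read as an estimate and a low count should not be taken as proof of safety.
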